# The With Or Without Olecranon K-wire (WOW OK) Trial of tension band wire fixation versus cerclage fixation without K-wires in displaced stable olecranon fractures: study protocol for a randomized controlled trial

**DOI:** 10.1186/s13063-023-07566-9

**Published:** 2023-08-29

**Keywords:** Olecranon fractures, Fractures, Bone, Ulna fractures, Wounds and injuries, Forearm injuries, Arm injuries

## Abstract

**Background:**

Displaced olecranon fractures with a stable elbow joint are classified as Mayo type 2a or 2b and are commonly operated with tension band wiring, i.e. two K-wires and a cerclage. Retrospective studies have reported fewer reoperations and complications with cerclage fixation alone when compared to tension band wiring, though with similar long-term results. We decided to compare tension band wiring to cerclage fixation of displaced, stable olecranon fractures in adults in a randomized controlled trial.

**Methods:**

All patients ≥ 18 years old with Mayo type 2a and 2b fractures presenting at Skåne University hospital will be eligible for study inclusion, unless exclusion criteria are met. Two hundred participants will be included and randomized 1:1 to cerclage fixation or tension band wiring.

Outpatient physiotherapist follow-up appointments will be scheduled at 2 and 6 weeks and at 3, 12, and 36 months at the Dept. of Orthopaedics. A lateral view radiograph of the elbow will be analysed at 6 months. The primary outcome of our study is the rate of reoperations. Secondary outcomes are complication rates, severity of complications, and patient-reported outcome measures (*Quick*DASH, Short Musculoskeletal Function Assessment, pain level, and patient satisfaction). The sample size was calculated to give 80% power for detecting a statistically significant difference in reoperation rates (with alpha-value 0.05), based on a previous retrospective study.

**Discussion:**

Reoperation and complication rates after tension band wiring of olecranon fractures are high. Treatment of these injuries is debated, and several ongoing trials compare tension band wiring with plate fixation, suture fixation, and non-operative treatment. As data from retrospective studies indicate that cerclage fixation may be superior to tension band wiring, we see a need for a randomized controlled trial comparing these methods. The WOW-OK Trial aims to obtain level-1 evidence that may influence treatment choice for this type of fracture.

**Trial registration:**

ClinicalTrials.gov NCT05657899. Registered on 16 November 2022. The trial complies with SPIRIT and CONSORT guidelines. The SPIRIT figure is found in Table 2.

**Supplementary Information:**

The online version contains supplementary material available at 10.1186/s13063-023-07566-9.

## Introduction

Olecranon fractures account for approximately 20% of all fractures of the proximal forearm [1]. Stable, undisplaced fractures are routinely treated non-operatively [2–4], while displaced fractures with instability in the ulno-humeral joint (so called trans-olecranon dislocations) are commonly operated with plate fixation [2, 5]. Displaced fractures that leave the elbow joint stable (Mayo type 2a and 2b) are often treated with tension band wiring (TBW) or plate fixation [2]. TBW is associated with soft tissue irritation, and high reoperation rates with hardware removal range from 25 to 84% in the literature [5–9]. Plate fixation has been associated with fewer reoperations but more severe complications compared to TBW in 2a and 2b fractures [10]. A Cochrane review from 2014 did not find any good support favouring either TBW or plate fixation over the other [11]. Nonoperative treatment of Mayo type 2a and 2b fractures yields acceptable outcomes in elderly patients with low functional demands but is not recommended to patients with moderate or high functional demands [12–15].

Previous retrospective studies at our department have shown that Mayo 2a and 2b fractures can be operated with cerclage fixation without K-wires (CF) yielding half the reoperation rate compared with TBW [7, 16]. To our knowledge, no other clinical studies have compared CF with TBW. As of 15 November 2022, there are 6 studies comparing treatments for olecranon registered on ClinicalTrials.gov. These included the following: one active and one completed study comparing TBW with plate fixation [17, 18], two active and one terminated study comparing surgical with non-surgical treatment [19–21], and one active study comparing TBW with suture fixation are registered [22]. Also, one active study comparing TBW with suture fixation is found in the International Standard Randomized Controlled Trial Number (ISRCTN) registry [23].

The controversy over treatment method for Mayo 2a and 2b fractures elicits the need to examine our research question: Is outcome following CF better than TBW for Mayo type 2a and 2b olecranon fractures? Our hypotheses are that CF will result in lower reoperation rate, complication rate, and intra-operative radiation time and exposure compared with TBW, while yielding non-inferior results in our specified secondary and tertiary outcome measures, including the patient related outcome *Quick*DASH. We aim to investigate this in a prospective 1:1 randomized controlled trial (RCT).

## Methods

### Trial summary

All patients presenting at Skåne University Hospital in Malmö or Lund with olecranon fractures of Mayo type 2a and 2b will be eligible for inclusion in the trial. Participants meeting exclusion criteria will be excluded. Informed voluntary written consent will be required for participation. Participants will be randomized 1:1 to surgery with CF or TBW.

Baseline descriptive data will be collected, and participants will be invited to a clinical follow-up at a physiotherapist outpatient clinic at the Dept. of Orthopaedics for collection of outcome measures at 2 and 6 weeks and 3, 12 and 36 months after surgery. The physiotherapist will be blinded to the treatment method of the participants. At 6 months, a lateral elbow radiograph will be performed and assessed for secondary dislocation and/or nonunion by an orthopaedic consultant.

The primary outcome measure is reoperation rates. Secondary outcome measures are complication rates and patient-reported outcome measures (PROM). Several tertiary outcome measures will be collected. Our hypothesis is that reoperation rates, complication rates, and intra-operative radiation time and exposure will be lower in the CF group while other outcome measures will be non-inferior for CF.

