### Blinding

Study participants will not be actively informed about which method was used but will be informed upon request. The physiotherapists measuring outcomes during follow-up will not be blinded to the treatment method; as they have access to the hospital files, a reliable blinding will be impossible to achieve in a cost-effective way. The physician assessing secondary dislocation or nonunion cannot be blinded as the treatment method will become apparent in the radiograph analysis. The study officials, surgeons, and other health-care providers will not be blinded. Data analysis will be performed on a blinded data set.

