### Follow-up

After surgery, follow-up will be identical in both study groups (Table 2). Standard peri-operative care will be given at the hospital.

**Table 2 Tab2:** Time-points for follow-up and data gathering, SPIRIT-figure

Activity	− 0.5 to 0	0	0.5	1.5	3	6	12	36
Inclusion, allocation, and randomization	x							
Intervention, both arms	x							
Primary outcome measures								
Reoperation rate				x	x		x	x
Secondary outcome measures								
Complication rate				x	x		x	x
Severe complication rate				x	x		x	x
QuickDASH				x	x		x	x
Patient satisfaction				x	x		x	x
Pain at rest				x	x		x	x
Pain in motion				x	x		x	x
SMFA		x					x	
Tertiary outcome measures								
ROM, flexion			x	x	x		x	x
Grip strength			x	x	x		x	x
Post-operative antibiotics				x	x		x	x
Secondary non union^a^			(x)	(x)	(x)	x	(x)	(x)
Sick leave				x	x		x	x
Fluoroscopy time		x						
Fluoroscopy DAP		x						
Operation time		x						

^a^The secondary dislocation or nonunion rate will be assessed from a lateral elbow radiograph at 6 months or will be recorded if diagnosed at any other time-point

In addition to descriptive baseline data, operation time, fluoroscopy DAP, and fluoroscopy time will be recorded. SMFA-questionnaires will be administered and collected by The Swedish Fracture Register (SFR) by mail shortly after the trauma (recall of pre-injury status), and 12 months later, and this data will be retrieved from SFR by the study officials.

At 2 weeks post-operatively, the cast will be removed, and a physiotherapist will record grip strength and ROM. Any reoperations, complications, ROM, grip strength, and return to work will be recorded at 6 weeks, 3 months, 12 months, and 36 months at the outpatient clinic at the dept. of Orthopaedics by a physiotherapist. PROMs (except SMFA) will be recorded by the participants in REDCap at the same time points. Reoperations and complications are recorded in each patient’s medical journal and subsequently retrieved by the study officials at interim analysis points and at the end of the trial.

At 6 months, a lateral view radiograph will be assessed by researchers DW and GC for any secondary dislocation or non-union. If secondary dislocation or nonunion is confirmed at any other point during the study, it will be recorded.

Any issue requiring additional follow-up or treatment will be handled in the standard health-care system which is public and tax-financed. After 36 months, the current follow-up will end.

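### The Trial summary calls the follow-up physiotherapist blinded and the Blinding section says the opposite; range of motion and grip strength cannot be reported as blinded assessments

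*Protocol article*

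**What the plan says.** The Trial summary sets up the visits: "participants will be invited to a clinical follow-up at a physiotherapist outpatient clinic at the Dept. of Orthopaedics for collection of outcome measures". Five time points are listed, the first two weeks after surgery and the last at 36 months. It then adds: "The physiotherapist will be blinded to the treatment method of the participants".

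The Blinding section states: "The physiotherapists measuring outcomes during follow-up will not be blinded to the treatment method". The reason follows directly: "as they have access to the hospital files, a reliable blinding will be impossible to achieve in a cost-effective way". On everyone else involved in care and study conduct it says: "The study officials, surgeons, and other health-care providers will not be blinded". It also says that the data set used for analysis will be blinded.

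The Follow-up section gives the physiotherapist's tasks. At 2 weeks, "a physiotherapist will record grip strength and ROM". After that, "Any reoperations, complications, ROM, grip strength, and return to work will be recorded at 6 weeks, 3 months, 12 months, and 36 months", again by a physiotherapist. It names a second source for events: "Reoperations and complications are recorded in each patient’s medical journal and subsequently retrieved by the study officials". Participants enter the patient-reported outcomes themselves in REDCap, except the SMFA, which comes by mail through the fracture register.

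**The concern.** A protocol cannot describe the same assessors as both blinded and unblinded. ROM and grip strength are readings taken by a person on a cooperating patient, so knowledge of the implant can influence them. The protocol plans to claim non-inferiority of cerclage fixation on these outcomes, and the Introduction reports that the department's own retrospective work favours cerclage. Assessor expectation is therefore a plausible source of bias.

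What is at stake is how the results may be described. A report that took its wording from the Trial summary would credit these outcomes with protection against detection bias that the Blinding section says the design does not have.

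**Working it through.** The point rests on text, not on a figure, so the check is a comparison of statements.

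1. **Same people, same role?** The Trial summary speaks of the physiotherapist at the outpatient clinic where outcomes are collected. The Blinding section speaks of the physiotherapists who measure outcomes during follow-up. The role and the visits are the same.

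2. **Is either sentence limited?** Neither is restricted to certain visits or certain outcomes.

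3. **Does other text reconcile them?** No. The section on trial status describes the current text as the first version, without amendments, so the difference is not a superseded passage. The blinded analysis data set protects the analysis and not the measurement.

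4. **Which statement is likely to be operative?** The Blinding section is the dedicated one and gives a reason, namely access to the hospital files. That reason, if true, defeats the Trial summary claim. The article does not say which sentence prevails, so the sponsor must confirm it.

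5. **Which outcomes depend on the answer?**

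| Outcome | Who supplies it | Effect of the contradiction |
|---|---|---|
| ROM: flexion, extension, supination, pronation (tertiary) | Physiotherapist; no other source named | Direct |
| Grip strength (tertiary) | Physiotherapist; no other source named | Direct |
| Reoperations (primary), complications (secondary) | Physiotherapist at four visits, and the medical journal via unblinded study officials | Smaller |
| Patient-reported outcomes | The participant | None |

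6. **Extent.** Four ROM measures plus grip strength make 4 + 1 = 5 outcomes. Each is recorded at five visits (2 weeks, 6 weeks, 3, 12 and 36 months), which gives 5 × 5 = 25 outcome-by-visit comparisons. Reoperations, complications and return to work are recorded at four visits, starting at 6 weeks.

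7. **Weight of those outcomes.** Table 1 gives a margin of 10 degrees for each ROM measure with power above 99%, and a margin of 5 for grip strength with power of 43% at n = 200 and 31% at n = 170. On the protocol's own figures, a firm non-inferiority conclusion is expected for ROM but not for grip strength. The blinding status therefore matters most for ROM.

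8. **Sample size.** It is built on reoperation rates of 13% and 27%. No blinding assumption enters it, so it does not change.

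**The case against.** The strongest reply is that the Trial summary is only a short overview, while the Blinding section is candid and explains itself. A reader checking the blinding would go there and be correctly informed. The outcomes that depend on the physiotherapist alone are mainly tertiary. They are measured to a national register's guidelines, with dynamometers calibrated at least once a year. Grip strength is already declared underpowered. Most of this stands, and it limits the weight of the point. It does not remove the contradiction: standardised measurement is not blinding, and the overview still states a protection that the design lacks.

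A reader might infer more than the text supports, in four ways.

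- **That protection of the primary outcome hangs on this sentence.** Reoperations and complications are also taken from the medical journal by study officials who are unblinded in any case. Blinding the physiotherapist would add little for these outcomes, whichever sentence is right.
- **That staff will behave differently depending on which section they read.** This is conjecture. The Blinding section describes a fact about file access, and the article does not show what visit instructions staff receive.
- **That leaving assessors unblinded is itself the error.** It is a design choice for which the protocol gives a reason. The error is the inconsistency.
- **That the REDCap visit form reveals the allocation.** The article does not say what the form shows.

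**Conclusion.** The contradiction is real, and nothing in the article resolves it. By the Blinding section's own reasoning, the Trial summary claim cannot be relied on. It is more than a clerical slip, because it decides how assessor-measured non-inferiority outcomes may be described. Its reach is limited: the effect is mainly on five tertiary outcomes at five visits, smaller on reoperations and complications, and absent for the self-recorded patient-reported outcomes and the sample size.

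The amount of bias cannot be derived from the document, and no figure is claimed for it. The conclusion assumes that the Blinding section describes actual practice, which the sponsor should confirm. The correction should be made, but the primary analysis does not depend on it.

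**What to change.** 1. Confirm with the sponsor what happens at the visits. Then correct the Trial summary sentence to agree with the Blinding section. The cost is one sentence.

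2. Describe ROM and grip strength as assessed unblinded in the analysis and in the report. This costs nothing beyond the wording.

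3. Optionally, ask the physiotherapists to take the ROM and grip readings before opening the surgical record. This addresses the route that the Blinding section names, access to the files, and needs a small change in visit order. It must not be presented as blinding. Participants are told their method on request and may disclose it, and an assessor may remember it from an earlier visit, so the protection is only partial. With recruitment expected to end in 2027 and follow-up in 2030, on that timeline the step could still cover many visits.

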### Null hypothesis

The null hypothesis in this study is that there is no difference in outcome measures at the follow-up time-points in adult participant with Mayo type 2a and 2b olecranon fractures treated with CF and TBW. Our alternative hypothesis is that CF yields superior results with fewer reoperations, fewer overall and severe complications, lower intra-operative radiation time and exposure, and non-inferior results in other outcomes.

### Objectives and outcome measures

The primary outcome measure is reoperation rates. A reoperation is cumbersome and costly and exposes the patient to additional risks associated with further surgical and anaesthesiologic procedures. Because of its significance for both patients and health-care systems, and as previous data indicate a large difference in reoperations between the two methods, reoperation rates was chosen as the primary endpoint.

The secondary outcome measures are:Complication rates based on a complication defined as any negative unexpected event attributed to the treatment.Severe complication rate is a constructed variable. Complications will be classified by the study official according to the modified Clavien-Dindo classification, a score specific for complications to orthopaedic surgery [24, 25]. Any complication of level 3a, 3b or higher is considered severe, thus creating a dichotomous variable (severe complication/not severe complication).The Quick Disabilities of the Arm, Shoulder and Hand score (*Quick*DASH) is a self-assessed questionnaire consisting of 11 items graded 1–5 assessing upper limb function for the affected arm, resulting in a 0–100 score [26]. It was chosen as it is a validated instrument [27], which is widely used throughout the literature, enhancing comparability of the results. The *Quick*DASH questionnaire performs similar to its full-length version the Disabilities of the Arm, Shoulder and Hand score [28].The Short Musculoskeletal Function Assessment (SMFA) questionnaire is a validated 46-item questionnaire used to assess overall musculoskeletal function [27, 29]. The result is converted to a 0–100 score with perceived function decreasing with increasing score. The interpretation of SMFA depends on translation and cultural adaptation. The Swedish adaptation is used in this trial, using bother (bSMFA) and dysfunction (dSMFA) indices as suggested by Williams [29].Overall satisfaction will be self-reported using a visual analogue scale (VAS) from 0 to 100. Zero corresponds to “completely satisfied” and 100 to “not satisfied at all”.Pain in rest and motion will be self-reported with VAS from 0 to 100. Zero corresponds to “no pain at all” and 100 to “worst imaginable pain” in the elbow.

The tertiary outcome measures are:Grip strength will be evaluated using a JAMAR dynamometer according to the guidelines from the Swedish national quality register for hand surgery (HAKIR) [30]. The dynamometers used will be calibrated at least once every year.Active postoperative range of motion (ROM) for extension, flexion, pronation and supination will be evaluated using the HAKIR guidelines [30].Secondary dislocation and/or nonunion rate will be assessed with a lateral view radiograph 6 months after the operation. In order to minimize radiation dose, only one radiograph and one view will be obtained. If secondary dislocation and/or nonunion is found, the participant will be referred to the standard healthcare system, and further investigation may include a full radiographic examination. Any demonstrated secondary dislocation and/or nonunion is regarded as a complication.Sick leave related to the elbow injury, counted in days.Intra-operative fluoroscopy radiation level will be measured as the dose area product (DAP) in mGy·cm^2^, and intraoperative fluoroscopy time will be measured in seconds. This will be recorded at the time of surgery from the fluoroscopy machine used. The model and make of the machine vary between operating rooms and may change during the study.Surgical time will be recorded in minutes during surgery counting from skin incision to the final suture of the surgical wound.Post-operative antibiotic treatment is defined as any prescribed antibiotic treatment related to the surgery after the intervention.

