**Secondary measures**										
Complication rate (yes/no)	> 99%	99%	68	0.22	0.18	0.16	0.15	18% vs 45%^a^	-	-
Severe complication rate (yes/no)	81%	75%	196	0.2	0.16	0.15	0.14	13% vs 27%^a^	-	-
* Quick*DASH (score)	94%	89%	138	12.9	10.5	9.9	9.1	13^c^	22^d^	14^e^
Patient satisfaction (VAS)	> 99%	> 99%	36	1.2	1	0.9	0.8	5^b^	2^b^	2^b^
Pain at rest (VAS)	94%	89%	138	1.2	1	0.9	0.8	1^b^	2^b^	1^b^
Pain in motion (VAS)	94%	89%	138	1.2	1	0.9	0.8	2^b^	2^b^	1^b^
bSMFA (score)	94%	89%	138	10.5	8.6	8.2	7.4	27^f^	18^f^	9^g^
dSMFA (score)	94%	89%	138	10.5	8.6	8.2	7.4	30^f^	18^f^	9^g^

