**Tertiary measures**										
ROM, flexion (degrees)	> 99%	> 99%	18	4.1	3.3	3.1	2.9	146^h^	7^h^	10^b^
ROM, extension (degrees)	> 99%	> 99%	10	2.9	2.4	2.2	2.1	− 3^h^	5^h^	10^b^
ROM, supination (degrees)	> 99%	> 99%	14	3.5	2.9	2.7	2.5	80^h^	6^h^	10^b^
ROM, pronation (degrees)	> 99%	> 99%	18	4.1	3.3	3.1	2.9	87^h^	7^h^	10^b^
Grip strength (newton)	43%	31%	352	9.4	7.6	7.2	6.6	32^i^	16^i^	5 ^j^
Post-operative antibiotics (yes/no)	< 1%	< 1%	6296	16%	13%	12%	11%	8%^a^	-	2%^b^
Secondary nonunion (yes/no)	< 1%	< 1%	9782	< 0.1%	< 0.1%	< 0.1%	< 0.1%	1%^k^	-	0.5%^b^
Sick leave (days)	< 1%^n^	< 1%^l^	30,790	18	14	13	12	35^b^	302	12
Fluoroscopy time (seconds)	< 1%	< 1%	3024	55	45	42	39	81^m^	94^m^	10^b^
Fluoroscopy DAP (mGy·cm^2^)	< 1%	< 1%	1492	19	16	15	14	25^m^	33^m^	5^b^
Operation time (minutes)	< 1%	< 1%	998	15	13	12	11	83^m^	27^m^	5^b^

Calculations of power and sample size requirements (n) for all outcome measures, including underlying assumptions. Previously published Minimally Clinically Important Differences (MCID) are given for outcomes where non-inferiority testing is performed and are used as non-inferiority margins in statistical analyses

^a^Based on a previous study at our institution [16]

^b^Based on estimations by the authors

^c^Based on QuickDASH following TBW [31]

^d^Based on unpublished data from a previous study where standard deviation (SD) was 22 for CF and TBW, although the sample was small

^e^Ranging from 3.5 to 19 points in the literature with a mean of 14 points [32–36]

^f^Based on outcomes following distal radius fractures as no elbow specific data was found in the literature [37]

^g^To our knowledge, no studies have reported MCID of SMFA following surgery for upper extremity injuries. The MCID was estimated to be half the standard deviation [38]

^h^Based on normal ROM [39]

^i^Based on data on elbow fractures [40]

^j^Based on a review of MCID of grip strength [41]

^k^Based on a study on the outcome of 196 olecranon fractures [42]

^l^Power if *n* = 100 and *n* = 85 as we expect half of the participant to work

^m^Based on data from all CF and TBW cases at our department during 2020

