### Statistical analysis

For power and sample size calculations, the alpha value was set to 0.05. Our hypothesis is that CF will yield lower reoperation and complication rates, lower intra-operative radiation, and less intra-operative fluoroscopy time; thus, one-sided tests of proportions were used for sample size requirements calculations [47]. For all other variables, tests for non-inferiority were used with assumed means for ratio scalar and interval variables and assumed proportions for nominal variables [47].

Statistical power and sample size requirements for demonstrating clinically significant differences between the groups were calculated using minimal clinically important difference (MCID) values from the literature. Power and sample size data, including relevant assumptions for all calculations, are presented in Table 1.

We expect ≥ 80% power for reoperation rates, complication rates, severe complication rates, *Quick*DASH, SMFA, patient satisfaction, pain in motion and at rest, and ROM. However, we do not expect to achieve 80% power for analysis of grip strength, postoperative antibiotics use, secondary dislocation or nonunion rate, sick-leave time, fluoroscopy time, fluoroscopy DAP, or operation time (Table 1).

The minimal detectable differences (MDD) for various outcomes and study sizes are presented in Table 1. For some of the secondary and tertiary outcome measures, the MDD is smaller than the MCID meaning that the study is under-powered for proving non-inferiority between the groups. Early termination of the trial resulting in a smaller sample size would further reduce MDD, hampering the power of the study.

The final study groups consist of all participants that complete the follow-up and participants that withdraw but permit analysis; see the section “ Post-inclusion withdrawals and exclusions”. The study groups will be compared using the chi-squared test for categorical variables (reoperation, complication) and Student’s *t*-test for continuous variables.

Comparisons between the study groups will primarily be performed by “intention to treat” analyses. If large cross-over between study groups occurs, “as treated” analyses will be performed as well. Subgroup analysis stratified by Mayo classification, age, gender, open fracture, and high energy trauma is planned for all outcomes.

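### The VAS non-inferiority margins in Table 1 appear to be on a 0-10 scale although the outcomes are collected on 0-100, and the protocol conflicts with itself on how non-inferiority is decided

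*Protocol article*

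**What the plan says.** Protocol article, Objectives and outcome measures, defines the two self-reported scales: "Overall satisfaction will be self-reported using a visual analogue scale (VAS) from 0 to 100", and "Pain in rest and motion will be self-reported with VAS from 0 to 100". On both, a higher score is worse.

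Table 1 (under Sample size) gives the planning values, with mean, SD and MCID as the last three entries of each row. One of the three VAS rows reads "Pain at rest (VAS) 94% 89% 138 1.2 1 0.9 0.8 1^b^ 2^b^ 1^b". The row for motion pain differs from it only in its mean, which is 2. The satisfaction row has mean 5, SD 2 and MCID 2, with power above 99% at both sample sizes and 36 participants needed for 80% power.

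The table states no scale for them. Footnote b attributes the values to the authors' own estimates. The legend says that the MCIDs "are used as non-inferiority margins in statistical analyses".

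The Introduction, Trial summary and Null hypothesis sections make non-inferiority of cerclage fixation (CF) the claim for the patient-reported outcomes. The Null hypothesis section nevertheless sets a single null of no difference for the outcome measures as a whole. Statistical analysis says non-inferiority tests underlie the power figures for these outcomes, but describes the comparison of the groups as follows: "The study groups will be compared using the chi-squared test for categorical variables (reoperation, complication". The t-test is the only method it names for the continuous outcomes. No margin, confidence limit or one-sided level appears there.

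**The concern.** A non-inferiority margin is the decision threshold, so its unit has to be that of the data. A pain margin of 1 means one tenth of a 0-10 scale but one hundredth of a 0-100 scale. If the Table 1 margins are carried unchanged into the analysis of 0-100 data, CF would have to be shown to be no more than one point in a hundred worse on pain, and two on satisfaction. A trial of this size could rarely show that.

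The second issue is which rule decides. The legend points to a comparison against a margin. The no-difference null and the plainly named tests point to a test of difference, which does not address non-inferiority. Non-inferior patient-reported results are part of the stated alternative hypothesis. If the unit or the rule is settled only after the data are seen, any such claim becomes post hoc.

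**Working it through.** **Inputs.** SD 2 and margins 1 (pain) and 2 (satisfaction) from Table 1; alpha 0.05 from Statistical analysis; 200 or 170 participants (100 or 85 per arm) from Sample size; true difference 0. Normal approximation, with SE = SD × √(2/n per arm).

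**Step 1: reproduce Table 1.** One-sided non-inferiority at 5%, power = Φ(margin/SE − 1.645), gives 97.1% and 94.7% for pain and a total of 100 for 80% power. That does not match. Two one-sided tests (equivalence) at 5% do match, with power = 2Φ(margin/SE − 1.645) − 1:

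- Pain, 100 per arm: SE = 2√(2/100) = 0.283; 1/0.283 = 3.536; Φ(1.891) = 0.9707; power 94.1% (stated 94%).
- Pain, 85 per arm: SE = 0.307; 1/0.307 = 3.260; Φ(1.615) = 0.9468; power 89.4% (stated 89%).
- Pain, n per arm for 80% power = 2[2(1.645 + 1.282)/1]² = 68.5, so 69 per arm and 138 in total (stated 138).
- Satisfaction, same formulas with margin 2: power >99% at both sizes and 36 in total (stated >99%, >99%, 36).

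These results depend only on margin/SD (0.5 and 1.0). They are right on any scale, provided margin and SD are both on the scale of the data.

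**Step 2: which scale?** The other 0-100 scores in Table 1 have SD 22 (*Quick*DASH) and 18 (SMFA), with MCIDs of 14 and 9. A VAS SD of 2 beside them fits 0-10. This is an inference from size.

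**Step 3: apply the margins literally to 0-100 data.** Assume SD 20 (ten times the table's 2) and a one-sided 5% non-inferiority test.

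| | Margin | 85 per arm (SE 3.068) | 100 per arm (SE 2.828) | Stated power (170 / 200) |
|---|---|---|---|---|
| Pain | 1 | Φ(0.326 − 1.645) = 9.4% | Φ(0.354 − 1.645) = 9.8% | 89% / 94% |
| Satisfaction | 2 | Φ(0.652 − 1.645) = 16.0% | Φ(0.707 − 1.645) = 17.4% | >99% / >99% |

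Range at 85 per arm for SD 10 to 30: pain 16.0% to 7.7%, satisfaction 36.7% to 11.3%. Under the two-sided equivalence formula that reproduces Table 1, power at SD 20 is zero, and 80% power would need 13,704 (pain) or 3,426 (satisfaction) participants.

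**Step 4: put both on 0-100.** SD 20 with margins 10 and 20 returns 94.1%, 89.4% and 138 for pain, and >99%, >99% and 36 for satisfaction, which are the stated figures. At one-sided 2.5% with 85 per arm, non-inferiority power for pain is Φ(3.260 − 1.960) = 90.3%.

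**Step 5: the decision rule.** Set side by side, the legend says the analyses use margins, the null hypothesis is no difference, and the analysis section names difference tests with no margin. The three cannot all describe how non-inferiority is decided.

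**The case against.** The case for leaving this alone has four parts.

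- **It is only a units slip.** Table 1 keeps SD and margin on one scale, so its power survives. That stands: a reader might infer that the trial really has 9% power for pain, but this arises only if an unscaled margin meets 0-100 data. The legend still makes the printed numbers the analysis thresholds, so the slip reaches the decision rule.
- **The document never says 0-10.** True. An SD of 2 on a 0-100 scale is arithmetically possible, though hard to believe beside SDs of 18 to 22. The authors have to confirm it.
- **No passage says that a non-significant test will count as non-inferior.** This also stands. A reader might infer that rule from the named tests, but the legend promises margins, and a t-test against a shifted null is a standard non-inferiority test. The harm under that inferred rule would also be uneven. With 170 participants and a true deficit equal to the margin, a two-sided t-test is non-significant in 9.7% of trials for pain (margin/SD 0.5), 1.4% for *Quick*DASH (14/22) and 46.9% for grip strength (5/16), which the protocol already declares underpowered. Nor could both harms befall the VAS outcomes: one needs the printed margin to be applied, the other needs it to be ignored.
- **The mechanics may sit in an analysis plan not at hand.** That excuses missing detail. It does not excuse passages within this document that disagree.

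**Conclusion.** Two limited defects hold. First, the VAS rows and the collected scale do not agree. Used as printed on 0-100 data, the margins leave about 9% power for pain and 16% for satisfaction at 170 participants, against the stated 89% and >99%. This rests on an assumed SD of 20, a one-sided 5% level and no true difference; an SD from 10 to 30 does not change the conclusion. That the table is on 0-10 is a strong inference, not a stated fact.

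Second, the protocol contradicts itself on whether non-inferiority is judged against a margin. It does not go so far as to equate non-significance with non-inferiority.

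Three secondary outcomes are touched by the scale problem, and all the non-inferiority outcomes by the conflict over the rule. The primary outcome, the sample size and the data collection are unaffected.

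**What to change.** 1. Have the authors confirm the scale of the Table 1 VAS rows. If it is 0-10, multiply mean, SD, MCID and MDD by 10: pain means 10 and 20, satisfaction mean 50, SD 20, margins 10 (pain) and 20 (satisfaction). The power and sample-size columns stay as they are.
2. In Statistical analysis, state that for the non-inferiority outcomes CF is non-inferior if the unfavourable confidence limit for CF minus tension band wiring lies inside the Table 1 margin. For the VAS outcomes that is the upper limit.
3. State the one-sided level openly: 5% to match the alpha of 0.05, or 2.5% (a two-sided 95% interval), which still gives about 90% power for pain at 170 participants.
4. Keep the difference tests for the superiority outcomes, and limit the no-difference null to them.

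Because the rule will rely on the Table 1 margins, check the *Quick*DASH row at the same time: its 94%, 89% and 138 correspond to a margin of 11 with SD 22, whereas the listed 14 would give a total of 86.

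The cost is three table rows and a few sentences, with no new data and no change to recruitment. It should be done before outcome data are compared by arm.
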